## Abstract

**Introduction:**

Patient-controlled admissions (PCAs) represent a change in psychiatric inpatient care where patients are allowed to decide for themselves when hospitalisation might be required. Prior research has demonstrated that PCA increase the number of admissions, but decrease days in inpatient care, while both the admissions to and days in involuntary care decrease. However, investigations have been restricted to specific patient groups and have not examined other possible benefits, such as effects on symptoms, quality of life and autonomy.

**Methods and analysis:**

This study explores the implementation process and effects of PCA in Region Stockholm, who is currently introducing PCA for all patients with severe psychiatric conditions and extensive healthcare utilisation. In total, the study comprises approximately 45 inpatient wards, including child and adolescent psychiatry. In a naturalistic evaluation, patients assigned PCA will be followed up to 36 months, both with regard to hospitalisation rates and self-reported outcomes. In addition, qualitative studies will explore the experiences of patients, caregivers of adolescents and healthcare providers.

**Ethics and dissemination:**

Approval has been granted by the Swedish Ethical Review Authority (Dnr: 2020-06498). The findings from this study will be disseminated via publications in international peer-reviewed journals, at scientific conferences, as part of two doctoral theses, and through the Swedish Partnership for Mental Health.

**Trial registration number:**

NCT04862897.

Strengths and limitations of this studyThis study will examine hospitalisation rates and self-reported outcomes for all patients assigned patient-controlled admissions (PCAs) in Region Stockholm, Sweden.Patient with different psychiatric disorders from approximately 45 inpatient wards with will be included and followed up to 36 months.For the first time, the implications of PCA for child and adolescent psychiatry will be investigated.Qualitative studies will explore the experiences of patients, caregivers of adolescents and healthcare providers.Due to ethical and judicial reasons, this study will not allow randomisation of patients or clusters, affecting the possibility of drawing causal inferences of outcomes.

## Introduction

Patients with severe psychiatric conditions, such as schizophrenia spectrum disorders, borderline personality disorder and eating disorders, often have care needs that warrant frequent admissions to inpatient care. Historically, it has been up to the healthcare providers to decide who and when to admit, sometimes referred to as the gate-keeper model. In essence, patients may seek care on their own, but the final decision to permit admission has always been made by a physician.^1^ However, recent trends towards patient participation and shared decision-making in healthcare has questioned this practice.^2^ In particular, the concept of patient-controlled admissions (PCAs) marks a dramatic shift in authority and increased partnership in psychiatric inpatient care, whereby patients are given the possibility of admitting themselves when needed. The basic premise is to identify and grant PCA to those who might benefit the most from its use as a way of preventing deterioration and novel bouts of illness and support patient empowerment. The procedures differ somewhat between settings and patient groups, but typically involves three to five inpatient days per stay, with or without restrictions regarding the number of admissions allowed per month.^1^

The effects of PCA have been examined in several studies. Early attempts of implementation were done in the USA and Australia, but the first large-scale investigations were made in the Netherlands, Norway, Denmark and Sweden.^3–10^ In sum, research indicates an increase in the number of admissions to inpatient care, but a decrease in the number of days in inpatient care. Meanwhile, both the admissions to and days in involuntary care decrease, suggesting that patients admit themselves more often, but require less fewer admissions of shorter duration, in line with the idea of using PCA to promote independence and increase help-seeking behaviours. However, apart from hospitalisation rates, self-rated outcomes have been far less explored. Aspects such as recovery and well-being do not demonstrate any significant changes, but self-report measures have been few and mainly focused on general functioning.^4 8 9^ Yet, qualitative studies imply that PCA can be beneficial in terms of increasing autonomy, agency, and well-being among patients. This is evident even in those cases where admissions are seldom or never used, suggesting that it might constitute a safety net for those at risk.^11^

PCA has been available since 2014 in Region Stockholm’s psychiatric care, which is Sweden’s largest hospital sector, but only for specific patient groups; schizophrenia spectrum disorders,^7^ eating disorders,^9^ and borderline personality disorder.^12^ Different procedures for using PCA have also been used depending on diagnosis, such as the length of each stay. However, following a resolution by the popularly elected Region Stockholm Assembly, the implementation of PCA will be completed in 2023 and involve patients with severe psychiatric conditions, irrespective of diagnosis, using the same procedures in the whole region. This will allow a large-scale implementation and evaluation of its effects, both in terms of hospitalisation rates and self-reported outcomes, up to 36 months following the assignment to PCA. A large number of patients with many different diagnoses will take part in several quantitative studies; including substance use, which has never been the subject to evaluation of PCA before. Furthermore, the use of additional self-report measures will permit an examination of its impact on symptoms, quality of life and autonomy. In addition, the implementation of PCA in child and adolescent psychiatry will be the first of its kind, making it possible to examine its potential effects among adolescents. Lastly, qualitative studies will examine the experiences of patients, caregivers of adolescents, and healthcare providers in an attempt to understand the use, and potential benefits and drawbacks of PCA. Overall, approximately 45 inpatient wards will eventually be included in this study, thus being, to the best of the authors’ knowledge, the largest attempt at defining the effects of PCA.

### Aims and objectives

The overall aim of this study is to assess the effects of implementing PCA throughout Region Stockholm, using a naturalistic prospective study design. This involves a number of quantitative studies which intend to understand the impact of PCA on hospitalisation rates and self-reported outcomes when introduced in psychiatric care. Qualitative studies will also be conducted to explore the experiences of both patients and healthcare providers with regard to its effects and use, including the perspective of caregivers of adolescents.

#### Primary research question

For patients with severe psychiatric conditions, identified as having extensive care needs and who have been assigned PCA by their healthcare providers; how will their hospitalisation rates change during the following 12, 24 and 36 months with regard to the number of admissions and days in inpatient care, and the number of admissions and days in involuntary care?

#### Secondary research question

Will hospitalisation rates differ between the various patient groups who have been assigned PCA?Will self-reported outcomes change following the assignment of PCA, that is, symptoms, quality of life and autonomy?Will self-reported outcomes differ between the various patient groups who have been assigned PCA?How are the healthcare expenditures for patients who have been assigned PCA affected, and do they differ between the various patient groups?What are the experiences of patients who have been assigned PCA for at least 12 months?What are the experiences of healthcare providers who have worked with PCA for at least 12 months?For adolescents, what are the experiences of caregivers to patients who have been assigned PCA for at least 12 months?For adolescents, will self-reported outcomes change in terms of their caregivers’ perception of the patients’ symptoms and quality of life?

In line with prior research, this study hypothesises that (1) the hospitalisation rates of patients will increase in terms of number of admissions to inpatient care, but (2) decrease in terms of days in inpatient care, as well as number of admissions and days in involuntary care. Furthermore, self-reported outcomes are expected to demonstrate (3) a decrease in symptoms and (4) increase in quality of life and autonomy. Lastly, qualitative investigations are believed to give a greater understanding of how patients, caregivers of adolescents and healthcare providers experience the use of PCA.

## Method and analysis

### Setting

This study is placed within the psychiatric care of Region Stockholm, which is the largest hospital sector in Sweden, serving a population of two million citizens. It is organised as nine public healthcare clinics, and four private healthcare clinics. One of these clinics constitute child and adolescent psychiatry, two concern eating disorders and two are dedicated to substance use disorders. One additional clinic is reserved for forensic psychiatry, but because its patients have been sentenced to care, these are not eligible to receive PCA. The 13 clinics that are included consist of approximately 45 inpatient wards and about 120 outpatient units that work together as pairs (ie, more than one outpatient unit can share the same inpatient ward). Each inpatient ward will in turn designate at least one bed for PCA. The healthcare providers consist of medical doctors and nurses with or without specialist training in psychiatry, mental health workers, counsellors, psychologists, psychotherapists, social workers, physiotherapists, occupational therapists and students undergoing basic or advanced clinical training in the field of medicine or psychiatry. The starting date of this study was 1 January 2022, and the planned end date is 31 December 2027.

### Patients

In Region Stockholm, PCA is assigned to those patients that have a severe psychiatric condition and who are deemed by their healthcare providers to warrant great care needs. Thus, eligible patients present with a documented history of recurrent admissions to inpatient care, a large number of days in inpatient care, or other indications of future hospitalisation. In order to determine eligibility, the following criteria are used by the healthcare providers:

Ongoing contact with an outpatient unit.An individual care plan and crisis plan.At least one episode of inpatient care during the previous 1-year period.Expected future need of inpatient care.Demonstrating an interest in and understanding the concept of PCA (for adolescents, this also includes their caregivers).

The inpatient wards include patients from general psychiatry (eg, schizophrenia spectrum diagnoses, neuropsychiatric disorders and anxiety disorders), geriatric psychiatry, affective disorders (eg, bipolar disorder), substance use disorders, personality disorders, eating disorders, and child and adolescent psychiatry (ie, up to 18 years of age).

### Procedure

Patients who are eligible to receive PCA are invited to a scheduled meeting with their healthcare providers from the outpatient unit and inpatient ward. The purpose and practice of PCA are then discussed verbally and information is provided in writing. Should the patient accept the offer, an agreement on the use of PCA is reached collaboratively and recorded in their medical records. For adolescents, caregivers also have to agree. Typically, PCA involves up to 4 days of inpatient care at a time, up to three times per month, although exceptions to the rule can sometimes be made. The agreement only covers 12 months at a time, after which it can be renewed at the yearly assessments. After the meeting, the patient receives all of the details in text and a printed copy of the agreement.

Each inpatient ward has allocated at least one inpatient bed for patients assigned PCA. Should a patient with an agreement wish to be admitted, they only have to contact the inpatient ward, any time of the day, any day of the week. In case the inpatient bed is already occupied, the patient is put on a waiting list. If more immediate care is required, the patient can always be admitted as usual. All admissions are managed by a nurse with delegated responsibility from the head of clinic. During admission, the patient is assessed with regard to suicidality, violence, and vital parameters, such as blood pressure and body temperature. Should there be an increased risk (eg, suicidal ideation and physical injury), regular intake is made. Once admitted, patients are offered care according to their specific needs and individual care plan. Consultation with a medical doctor is possible, but not part of usual practice. The patient is also free to discharge at will, which is also handled by a nurse; however, should the patient warrant further stay at the inpatient ward, a medical doctor can decide if regular admittance is necessary.

Since PCA is part of regular healthcare, patients can always agree to its use but refuse to participate in the present research study. The offer to take part in a study on the effects of PCA is always made after the use of PCA first has been agreed on, whereupon the objectives of this study is discussed verbally and information is provided in writing. Informed consent is required and documented in the medical records. For adolescents, informed consent needs to be signed by both the adolescent and all caregivers (eg, legal parents, custodians or other entities responsible for the patient’s care). Following this, the patient completes the self-reported outcome questionnaires that are included in the study, as reviewed below. For adolescents, this also involves the caregivers’ perception of the patient’s well-being. All of the self-reported outcome questionnaires are then completed at the mandatory yearly assessments, except for the Visual Analogue Scales (VAS) that are administered each month via SMS (more information provided under self-reported outcomes). This is in line with the procedures surrounding the use of PCA in Region Stockholm, where mandatory yearly assessments are made to check-up on patients’ health status and whether or not PCA should be continued. This is also believed to improve data collection as it does not require paper-and-pencil administration or letters.

The implementation of PCA throughout Region Stockholm is coordinated and supported by the Centre for Psychiatry Research, which is a R&D centre run jointly by Karolinska Institutet and the hospital sector. The Centre for Psychiatry Research performs an assessment of the risks and needs of each outpatient unit and inpatient ward, and provides training and supervision regarding all of the PCA routines. This consists of an online course and a half-day on-site workshop, and the latter of regular meetings with all of the healthcare providers. The Centre for Psychiatry Research is also responsible for evaluating the effects of PCA and has a research steering group consisting of the authors of the current study protocol. These range from doctoral candidates to senior-level researchers with comprehensive experience of conducting both quantitative and qualitative studies in a psychiatric setting.

### Study design

This study will evaluate the effects of PCA in Region Stockholm in collaboration with the Commissioner of Healthcare. This follows a resolution made by the popularly elected Region Stockholm Assembly, which means that both the implementation and policy surrounding PCA have already been decided. Hence, according to the decision, all patients with severe psychiatric conditions who are considered by their healthcare providers to have great care needs will be offered PCA as long as the criteria mentioned above are fulfilled. Furthermore, because the primary objective of the PCA programme is the provision of healthcare and not research, a more complex study design using randomisation on an individual or clinic level (ie, cluster) is not allowed due to ethical and judicial reasons. Hence, this study is restricted to a naturalistic prospective study design. Patients are followed for 12, 24 and 36 months using their medical records to check changes in hospitalisation prior to (pre) and following inclusion in the PCA programme (post), similar to what has been done previously.^7^ For example, patients who are included in November 2021 may have hospitalisation rates retrieved from the period November 2018–2020 and compared against hospitalisation rates from the period November 2022–2024, depending on the availability of historical data. In terms of self-reported outcomes, patients complete the measures when being assigned PCA and at the yearly follow-up assessments, with the exception for the VAS that is administered monthly via SMS. However, in these specific cases, historical data do not exist as these measures have not been collected previously. Only patients with no previous use of PCA when they consent to take part in this study will be analysed, as recorded in their hospital records.

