### Sample size calculation

This study intends to examine the impact of introducing PCA in psychiatric care in Region Stockholm. As such, only patients who are assigned PCA and have consented to take part in the research are included. An a priori sample size calculation, which is typically used to estimate an adequate sample size for subsequent recruitment, is thus not informative. However, based on previous experiences of introducing PCA in the region, it is reasonable to expect about twelve patients per inpatient ward who consent to participate, which would amount to a total sample size of 564.^7^ When calculating the standardised effect size possible to detect under these circumstances, based on the difference between two dependent means, and using a probability level of 0.05 and a power of 0.80, the result is Cohen’s *d* of 0.12, which is a small, although clinically relevant effect for a population of patients with severe psychiatric disorders, and in line with similar findings on self-reported outcomes.^4 8 9^

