### Statistical analysis

Previous studies on the use of PCA have demonstrated that hospitalisation rates are seldom normally distributed. In essence, few patients will use the possibility to admit themselves to inpatient care, resulting in data that is positively skewed and has a leptokurtic distribution. Investigating whether assumptions of normality are violated will therefore be essential prior to any statistical analysis, whereby suitable means of analysing the data will be employed, that is, non-parametric tests or bootstrapping procedures. As for the self-reported outcomes, no prior evidence seems to suggest that data will not be normally distributed. Here, conditional changes over time will instead be modelled using a mixed models-approach, that is, multilevel models. All analyses will be made according to an intention-to-treat principle, accounting for those values that have been lost via multiple imputation or maximum likelihood estimation. Likewise, all analyses will control for potential confounders, such as hospitalisation rates prior to PCA and self-reported outcomes when assigned PCA, as well as demographics available in the hospital records, for example, age, gender, civil status, children and psychiatric disorders.

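### The primary before/after comparison of hospitalisation lets any regional calendar trend into the estimated PCA change, and no adjuster named in the article removes it

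*Protocol article*

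**What the plan says.** The primary research question asks how admissions and days, in inpatient and in involuntary care, change over 12, 24 and 36 months after PCA is assigned. Under Study design, records are used "to check changes in hospitalisation prior to (pre) and following inclusion in the PCA programme (post"). There is no concurrent comparison group for these outcomes. The one worked example takes a patient included in November 2021 and sets November 2018–2020 against November 2022–2024, subject to what historical data exist.

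Under Statistical analysis, hospitalisation is to be analysed with non-parametric tests or bootstrapping. All analyses adjust for possible confounders. Those named are hospitalisation before PCA, self-report at assignment, and "demographics available in the hospital records, for example, age, gender, civil status, children and psychiatric disorders". The list is open, but calendar time or period is not mentioned anywhere in the article.

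On dates, the Setting section says: "The starting date of this study was 1 January 2022, and the planned end date is 31 December 2027". The Introduction says that "the implementation of PCA will be completed in 2023". Registry-matched patients appear only in the cost-utility paragraph. The strengths and limitations box concedes that causal inference is limited because randomisation is not possible. The aim is nevertheless to assess effects, and the hypotheses are directional: admissions up; inpatient days, involuntary admissions and involuntary days down.

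**The concern.** In this contrast every patient moves forward in calendar time, and nobody is observed over the same dates without PCA. Anything that changes bed use or involuntary care across the region between the two windows is therefore added to the PCA estimate. A falling trend would help produce the hypothesised falls in days and involuntary care, and would work against the hypothesised rise in admissions. A rising trend would do the reverse.

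The windows move further apart as the horizon lengthens, so the carry-over grows from 12 to 36 months. With no PCA effect at all, the results could look like an effect that builds up over time. This bears directly on how the primary question can be answered.

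**Working it through.** **1. The plan's own figure.** The Sample size calculation section works "based on the difference between two dependent means", "using a probability level of 0.05 and a power of 0.80", with a sample "which would amount to a total sample size of 564". Sidedness is not stated. Two-sided, d = (1.960 + 0.842)/√564 = 2.802/23.75 = 0.118, which rounds to the article's Cohen's d "of 0.12, which is a small, although clinically relevant effect". The figure is reproduced. It rests on a paired comparison with no control group, so drifts of similar size matter.

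**2. Why the named adjusters do not help.** Write a patient's change as Δᵢ = τ + δ + β′(xᵢ − x̄) + eᵢ, where τ is the PCA effect, δ the calendar shift shared by all, and xᵢ the patient's values at or before assignment. The covariates can explain which patients change more. The average change is still τ + δ, whatever β is.

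**3. Distance between the windows.** Equal windows of h years that meet at inclusion have midpoints h years apart: 12, 24 and 36 months. This layout is an assumption. Read literally, the worked example has midpoints at November 2019 and November 2023, which are 48 months apart.

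**4. Carry-over with no PCA effect.** The regional trend g is not in the article and is assumed. Apparent rate ratio = (1 + g)^h:

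| g per year | 12 months | 24 months | 36 months | 48 months (literal example) |
|---|---|---|---|---|
| -2% | 0.98 | 0.96 | 0.94 | 0.92 |
| -5% | 0.95 | 0.90 | 0.86 | 0.81 |
| +2% | 1.02 | 1.04 | 1.06 | 1.08 |
| +5% | 1.05 | 1.10 | 1.16 | 1.22 |

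**5. Against the planned sensitivity.** Suppose the SD of the paired difference is 1.5 times the mean (assumed). At -5% per year the 36-month drift is 14.3%, so d = 0.143/1.5 = 0.095, and a nominal 5% paired test on 564 patients rejects with probability 0.62. At -3% per year d = 0.087/1.5 = 0.058 and the probability is 0.28. Over trends of -1% to -5% per year and SD/mean from 1 to 2, the 36-month probability runs from 0.06 to 0.92. This uses the paired-means test of the sample size section; the planned hospitalisation analysis is non-parametric or bootstrapped, so the figures are only indicative.

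**6. Can inclusion dates separate trend from effect?** With 36 months of follow-up ending in December 2027, inclusion can run to about December 2024. A noise-free patient-by-quarter panel was fitted with 36 months either side of inclusion, patient effects, terms for PCA years 1 to 3, a trend of -3% per year and a true effect of zero.

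- Without calendar terms, the apparent effect in years 1, 2 and 3 is -5.9%, -8.7% and -11.5%. The midpoints here are 2, 3 and 4 years apart, because each post year is set against the whole pre period.
- With calendar-quarter terms and inclusion spread over 24 or 36 months, it is 0.0% in every year. With a single inclusion date it is not identified.
- The Patients section requires an inpatient episode in the year before inclusion. If that doubles the rate in that year (assumed), the apparent effect is -25% to -30% without calendar terms and -55% to -73% with calendar terms alone. Adding a term for that year returns 0.0%.
- With that term, calendar adjustment multiplies the standard error by 2.4 to 2.6 in year 1 and 4.2 to 4.5 in year 3, assuming independent quarterly errors.

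**The case against.** The strongest reply is that this is an omission rather than an error. The confounder list is open, a full protocol or SAP could add calendar time, the primary question is worded as change, and the article admits limited causal inference. Part of this stands: nothing excludes a calendar adjustment. But the article itself fixes an uncontrolled within-patient contrast and names a confounding strategy that misses the confounder to which such a contrast is most exposed. A general caveat adjusts for nothing.

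Second, no trend is documented, so materiality is not shown. That stands for size and sign. A reader might infer from the dates that pandemic years or a later rebound distort the pre windows; the article has no regional series and says nothing of the kind.

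Third, calendar time is not the only thing that differs between the windows, and perhaps not the largest. Selection on a recent admission raises the pre window, and under the doubling assumption above it outweighs the trends considered. This stands. It is a separate bias, which a calendar adjustment does not cure.

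Fourth, a reader might infer that staggered inclusion makes separation easy and cheap. The article does not present staggering as a design feature; it is inferred from the dates. Calendar terms alone can worsen the bias, and the loss of precision is large. An unadjusted regional series would also contain PCA patients and absorb part of any real effect. These points shape the fix but leave the gap in place.

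**Conclusion.** The point holds in limited form. The primary hospitalisation estimate is the PCA change plus any calendar shift common to the region, and no named adjuster removes the second part.

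The ratios in the table rest on an assumed trend and, up to 36 months, on equal windows that meet at inclusion. Taking the worked example literally moves them further from 1. Under a constant trend the distortion grows about threefold from 12 to 36 months.

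The article does not support saying that a trend exists, that it favours PCA, or that the planned result will be spurious. What follows is that the analysis as described cannot tell a regional trend from a PCA change, and that a cheap check would show how far this matters. It should be made, but as a sensitivity analysis rather than a replacement for the primary analysis.

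**What to change.** Add to Statistical analysis:

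- **Regional offset, as a sensitivity analysis.** For each patient and window, divide the observed admissions, inpatient days, involuntary admissions and involuntary days by the regional rate summed over the same months. Compare the pre and post ratios with the same test or bootstrap as the main analysis, and report results with and without the offset. Exclude patients coded as PCA from the regional series for all months, not only after inclusion, so that its make-up does not change as they join. The Hospitalisation rates section says that coding exists to identify them.
- **Matched comparison.** Where registry data allow, extend the matched patients of the cost-utility paragraph to the hospitalisation outcomes.
- **Optional calendar-period model.** If dated person-time is modelled, include a separate term for the year before inclusion.

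The cost is one aggregate series to extract (its availability is assumed) and a few lines of text. Some dilution remains if PCA patients are not fully removed, for example those who use PCA but decline the research, if the coding does not cover them. The offset leaves selection on a recent admission uncorrected. The optional model widens intervals greatly: the standard error is about 2.5 times as large in year 1 and over 4 times in year 3.
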